**Table Taba:** 

Zα/2 = critical value of the normal distribution at α/2; α = 0.05	1.96
Zβ = critical value of the normal distribution at β; β is 0.2	0.84
p0 = expected proportion of referrals eligible for PC+ at baseline	0.12 (12%)
p1 = expected proportion of referrals eligible for PC+ 1 year after the intervention is implemented	0.06 (6%)
p = (p1+ p0)/2	0.090
r = ratio of patients per group	1

### Planned statistical analysis

In general, the continuous outcome measures will be expressed in means, medians and standard deviations and the categorical variables in numbers and percentages.

#### Descriptive statistics

Demographic data (e.g. gender, age, level of education, nationality and co-morbidities) will be described for the total group and for the intervention and control group, separately. The two groups will be tested on differences between characteristics, using the t-test for continuous variables and the chi-square test for categorical variables. If variables differ between the two groups, with a *p*-value ≤0.10 they are considered to be potential confounders in further analysis.

#### Data analysis

To investigate the effect of PC+ on population health, patients’ experience of care and health-care costs an intention to treat analysis will be conducted. The between-group comparisons will be analysed with multilevel analysis to account for the dependency of observations in time. We will apply a two-level linear mixed model (time, participants) and the level of statistical significance will be set at 0.05 (two-tailed). Separate models (random intercept) will be set up for each outcome measure. The independent variables in each model are a dummy variable indicating the group (control group = reference category), three dummy variables for time (T0 = reference category) and the interaction variable between group and time.

To correct for the possible confounding influence of baseline characteristics of the patients (e.g. age, gender, level of education, native country and health-care costs) and the GP characteristics (e.g. age, gender and practice) a propensity score will be added into the multilevel model. The propensity score will be estimated using a logistic regression model with treatment group (control or intervention) as dependent variables and baseline variables (patient and GP characteristics) included as independent variables. Only baseline variables that are related to the outcome variable (with a *p*-value smaller than 0.10) are included in the propensity score [25].

If normality assumptions are violated, outcome variables will be log-transformed and if necessary non-parametric tests will be used.

SPSS version 22 is used to analyse the data.

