### Objectives and underlying premises of PC+

This overall study aims to evaluate the effects of cardiology PC+ centre on the Triple Aim outcomes. The underlying premises of the researchers on the effects of the intervention are that the cardiology PC+ centre will result in an (at least) equivalent health of the population, improved quality of care as experienced by patients and a reduced number of referrals to hospital-based outpatient cardiology care, and hence reduced health-care costs.

The underlying premises are grounded on several hypotheses. Firstly, it is supposed that the health of the study population (patients with non-acute and low-complexity cardiology complaints) will be at least the same, since the patients receive the same diagnostic tests and the care is provided by health-care professionals with the same level of expertise. Thus, the cardiology PC+ centre and hospital-based outpatient cardiology care will lead to the same health outcomes. After the introduction of PC+, the patients who need more specialized hospital care are likely to be referred by their GP to the hospital and the patients who do not need hospital care will remain in primary care.

Secondly, the aim of the introduction of PC+ is to improve patients’ experience of care. In this study the component patients’ experience of care is based upon the six dimensions of health-care performance of the Institute of Medicine (IOM), which partially overlaps with the last premise about health-care costs [19]. It is supposed that PC+ will improve: 1) the effectiveness of care since PC+ will result in fewer unnecessary referrals to hospital-based outpatient cardiology care, thus less overuse of care, 2) the timeliness of care since PC+ will decrease the waiting time, 3) the patient-centredness of care since an underlying rationale of PC+ is being respectful and responsive to individual patient preferences, needs and values, and 4) the efficiency of care since PC+ will result in less waste of expensive hospital-based outpatient cardiology care. Efficiency of care is related to health-care costs, therefore it will be included in this dimension. In addition, it is supposed that PC+ has no effect on the level of 5) safety of care and 6) equity of care and thus it is supposed that these will remain at the same level.

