### Sub-study 1: the quantitative study

#### Aim

The aim of the quantitative part is to measure the effects of the PC+ intervention on the population’s health, patients’ experience of care and health-care costs. To measure the effects the researchers will use the following sources: patient questionnaires, data from the cardiology PC+ centre, data from the regional hospital and health insurance claims data. The data will be collected at four different time points, namely at baseline, before the patient has the first consultation with the cardiologist (T0), a week after the first consultation (T1), 3 months after the first consultation (T2) and 6 months after the first consultation (T3). The outcome parameters, including the dimensions, outcomes, concepts, methods and time frame, are summarized in Table 1.

**Table 1 Tab1:** Overview of the outcome measurements

Dimension	Outcome measure	Concept	Method	Data collection time			
				T0	T1	T2	T3
Population’s health	Health status, health-related quality of life	EQ-5D-5 L	Questionnaires	X	X	X	
		EQ-VAS		X	X	X	
		SF-12		X		X	
Experience of care	Effectiveness	EQ-5D-5 L	Questionnaires	X	X	X	
		Number of referrals	Data^a^	X		X	X
	Timeliness	Time between referral of the GP and appointment at the PC+ centre/hospital	Questionnaires	X	X		
	Patient centred	Questions about the experiences of patients with health care	Questionnaires		X		
	Safety	% Hospital admissions	Data^a^				X
		% Emergency care visits					X
	Equity	Subgroup analysis, e.g. educational level and age	Questionnaires	X		X	
Health-care costs	Health-care costs: primary care, PC+, secondary care and diagnostics	Health insurance claims data	Data^a^				X
	Efficiency	Number of consultations	Data^a^				X
		% Hospital admissions					X
		% Patients referred to hospital after PC+					X

T0 – at baseline: before the consultation

T1 – within a week after the consultation

T2 – 3 months after the consultation (follow-up)

T3 – 6 months after the consultation (follow-up)

^a^Data of the PC+ centre, the hospital and Vektis

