### Study population

The study population consists of adult patients (≥18 years) with non-acute and low-complexity cardiology-related health complaints, registered with a GP in the region of the pioneer site. Based on the principles of shared decision-making the GP and the patient will discuss the options for referral which will be either the PC+ centre (intervention group) or the hospital-based outpatient cardiology care (control group). The decision will be based on expertise and experience of the GP, the severity of the complaints of the patient and the preferences of the patient. Less sever, non-acute and low-complex patients should be referred to PC+. At the moment, no specific criteria are included for the referral to PC+. The GP is in charge of referring a patient to the PC+ centre or the hospital-based outpatient cardiology care, i.e. the researchers do not have any influence on the referrals.

Excluded from participation are patients who are already diagnosed with cardiology-related health problems by a cardiologist and patients who have received balloon angioplasty or bypass surgery in the past 18 months. Furthermore, patients with acute health problems who require immediate hospital care and/or patients arriving at the emergency department of the hospital are excluded from participation.

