### Recruitment of patients

Regarding the allocation of patients, this is a practice-based study and therefore the allocation of patients is not random but based on the decision of the GPs. The patient enrolment of both the intervention group and the control group starts when a GP refers a patient to PC+ or hospital-based outpatient cardiology care. Furthermore, it will be statistically tested whether the groups differ in patients’ characteristics at baseline. In case the there is a difference in patients’ characteristics at baseline, the propensity score method (PSM) is used to statistical control for the differences [25]. In addition, the GP will inform all patients about the study. Before the consultation at the PC+ centre or the hospital the patients will receive an information letter with an informed consent form. In this letter they are asked if they would like to participate in the study. All eligible patients have to give informed consent. The flow of participants and the time of measurements, i.e. data collection, are summarized in Fig. 2.

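### Patients are grouped at GP referral, but T1 and T2 are dated only from the first consultation: never-seen patients have no scheduled follow-up questionnaire, and the T0–T2 interval may differ by group

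*Protocol article*

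**What the plan says.** All of this is in the protocol article.

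- **Group and enrolment.** Under Recruitment of patients: "The patient enrolment of both the intervention group and the control group starts when a GP refers a patient" to one of the two settings. The same section says that "the allocation of patients is not random but based on the decision of the GPs".
- **Consent.** It is sought between referral and consultation: "Before the consultation at the PC+ centre or the hospital the patients will receive an information letter with an informed consent form".
- **Follow-up clock.** The Aim of sub-study 1 sets the later time points at "3 months after the first consultation (T2) and 6 months after the first consultation (T3"). T1 falls within a week after the consultation. The Patient questionnaire section and Table 1 use the same clock. T0 has no anchor beyond preceding the consultation.
- **Expected wait.** The Objectives section predicts an improvement in "the timeliness of care since PC+ will decrease the waiting time", and the wait from referral to consultation is itself an outcome.
- **Analysis.** Under Data analysis, "an intention to treat analysis will be conducted", using a random-intercept linear mixed model with dummy variables for time (T0 as reference) and a group-by-time interaction. The missing-data section says that missing follow-up is not imputed and is left to the multilevel model.

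**The concern.** An analysis by intention to treat should measure outcomes in everyone who entered a group, whatever happened next. Here a patient enters at referral, but the post-baseline questionnaires are triggered by a later event, the consultation. Whether that event happens may depend on how the patient fares while waiting, and the plan expects the wait to depend on the group.

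For patients who are seen, there is a related timing problem. The change from T0 to T2 includes whatever part of the wait follows the T0 questionnaire. The model codes T0 and T2 as nominal visits, so a different elapsed time in the two groups would be absorbed into the group-by-time term.

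At stake is the health comparison (EQ-5D-5L, EQ-VAS, SF-12), where the plan's premise is that PC+ is at least equivalent. A small bias in either direction matters more for such a premise than for a large expected difference.

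**Working it through.** The plan gives no figure on this point to reproduce. The only document number used is the target of 429 patients per group, which is 358 × 1.2 = 429.6, rounded down in the plan. Waits, non-attendance rates and recovery rates are not in the documents; those below are assumptions chosen to show a range.

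**Step 1: who can have a T2 measurement.**
- Date of T2 = date of first consultation + 3 months.
- Without a consultation this date is undefined, although the patient has a group (from referral) and may have consented and completed T0.
- Such a patient contributes a T0 row only. This row informs the T0 mean and, through the random intercept, slightly informs T2. It adds almost nothing to the group-by-time contrast.

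Patients able to have T1 and T2 = 429 × (1 − assumed non-attendance):

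| Non-attendance PC+ / hospital (assumed) | PC+ | Hospital |
|---|---|---|
| 2% / 2% | 420 | 420 |
| 2% / 5% | 420 | 408 |
| 5% / 10% | 408 | 386 |
| 5% / 15% | 408 | 365 |

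**Step 2: the T0–T2 interval for those who attend.**
- T0–T2 = (days from T0 to consultation) + 91.
- The group difference is therefore the difference in days from T0 to consultation.

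| Wait PC+ / hospital, days (assumed) | T0–T2 if T0 is at referral | Difference | Difference if T0 is 3 days before consultation |
|---|---|---|---|
| 7 / 14 | 98 / 105 | 7 | 0 (94 / 94) |
| 7 / 28 | 98 / 119 | 21 | 0 |
| 14 / 42 | 105 / 133 | 28 | 0 |
| 14 / 70 | 105 / 161 | 56 | 0 |

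The article's wording allows both columns and anything between them.

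**Step 3: what an interval difference could do to EQ-5D.**
- Suppose untreated recovery is linear and amounts to 0.03 to 0.05 over 91 days (assumed).
- Spurious difference = (recovery / 91) × difference in interval.
- 0.03 / 91 × 14 = 0.005; 0.05 / 91 × 28 = 0.015; 0.05 / 91 × 42 = 0.023.
- With a longer hospital wait this would favour the control group. With T0 tied to the appointment it is zero.

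**Step 4: direction of the non-attender effect.**
- If patients with a longer wait recover and do not attend, their improvement goes unobserved and the control group looks worse than it was.
- If they deteriorate and are treated elsewhere, the control group looks better than it was.
- The two can offset each other or the interval effect, so the net sign cannot be stated.

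**The case against.** The strongest reply is that dating follow-up from the consultation is a legitimate choice when two consultation settings are compared, and that the definition of the analysis set belongs in a fuller document that is not shown. Both points are fair. The silence on the analysis set is not the finding. The finding is the clock that the article does fix: it leaves consenting non-attenders without a T2 date, and no later definition can recover a questionnaire that was never sent. The 20% dropout allowance replaces numbers; it does not correct selection.

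Several stronger readings are tempting, but the documents do not support them:

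- **Non-attenders vanish from the analysis.** They do not. With a T0 questionnaire they remain in the mixed model in their referral group, under missing-at-random. A patient who recovers before consenting was never a participant.
- **The intervals do differ by group.** Nothing says that T0 is completed near referral. The supported wording is that they may differ.
- **Events during the wait are lost from every outcome.** T3 carries no questionnaire, and the sections on hospital data and claims data both start collection at referral. Table 1 and the Health-care costs section count the six months from the consultation instead. That inconsistency is a separate matter and needs reconciling.
- **The emergency exclusion removes enrolled patients.** The sentence that "patients arriving at the emergency department of the hospital are excluded from participation" sits among the entry criteria. Emergency visits are also a planned six-month outcome, so it reads naturally as applying at entry.
- **T2 should move to a fixed interval after referral.** That would make time since consultation differ by group instead, which is a trade-off and not a correction.

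**Conclusion.** The concern holds for the questionnaire outcomes. Group is set at referral and follow-up is triggered by the consultation, so the intention-to-treat comparison of health change rests in practice on consenting patients who attend, with missing-at-random covering the rest. That assumption is open to doubt because recovery or deterioration during the wait is a plausible reason for not attending.

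The timing part is conditional. The group difference in the T0–T2 interval lies between zero and the full difference in wait, depending on when T0 is filled in, which the article does not fix.

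The EQ-5D range of 0.005 to 0.023 illustrates the interval effect alone. It rests on an assumed recovery rate, T0 at referral, and hospital waits 14 to 42 days longer. The number of never-seen patients may be small. Neither the size nor the net direction of the combined bias follows from the documents. The point merits a change because the remedy is cheap during data collection and cannot be applied afterwards.

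**What to change.** 1. **Aim of sub-study 1 and Patient questionnaire:** send the T2 health questionnaire to every consenting referred patient. For those who do not attend, date it from the booked appointment. T1 stays tied to the consultation, since it asks about the experience of care.
2. **Data analysis:** state that all consenting patients are analysed by first referral destination, whether or not they were seen.
3. **Data collection and Data analysis:** record the actual completion dates of T0 and T2, and include actual elapsed time in the health models, at least as a sensitivity analysis. Because elapsed time contains part of the wait, which PC+ is meant to change, report results with and without this term.

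The cost is a few extra mailings, access to the appointment date for non-attenders, and one more model term. The consultation-based T2 for attenders does not change.

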The practice-based study focuses on a cardiology Primary Care Plus (PC+) centre. In this pioneer site PC+ implies substitution of specialist care in the hospital setting with specialist care in the primary care setting and it is designed for patients with non-acute and low-complexity related health complaints. Since virtually all specialists are hospital-based in the Netherlands, PC+ is a new form of health care. In the cardiology PC+ centre cardiologists provide consultations in the primary care setting. During the PC+ consultation the patients receive a comprehensive screening and afterwards the cardiologist sends his recommendations for further treatment (if needed) to the GP. For example, the specialist informs the GP about whether a referral to hospital care is needed. Based on the recommendation, the GP discusses the options for further treatment with the patient. Moreover, within PC+ the GP remains clinically in charge of the patient. PC+ strengthens the gatekeeping and coordinating role of the GP by intensifying the collaboration and communication between the specialists and the GPs. The PC+ intervention aims to improve the health of the population and patients’ experience of care and to reduce the number of referrals to hospital care (as well as hospital-based outpatient specialist care) in order to reduce health-care costs growth. In this study, the PC+ intervention is compared to care-as-usual, both are described in detail in the methods section. This paper describes the design of the evaluation of the cardiology PC+ intervention, combining qualitative and quantitative methods.

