#### Experience of care

The experience of care will be measured using the perspective of the patient, i.e. the patient’s interaction and experience with the health-care system. The outcome parameters are based upon the six dimensions of health-care performance of the IOM: safety, effectiveness, equity, timeliness, patient-centredness and efficiency [19]. As mentioned above, efficiency will be included in the dimension health-care costs.

Effectiveness of care will be measured with the EQ-5D-5 L questionnaire and the percentage of referrals to hospital-based outpatient cardiology care. On the one hand, effectiveness will be measured using the EQ-5D-5 L scores, where it is analysed whether the health of the population is improved after a follow-up of 3 months. On the other hand, effectiveness will be measured using the number of referrals to hospital-based outpatient cardiology care, where it is analysed whether this number is decreased in the period from 2013 to 2017.

Timeliness of care will be examined by measuring the waiting time (in days) between the day the patient is referred by his GP and the day of the first consultation with the cardiologist.

Patient-centred care will be measured using items based on the Consumer Quality (CQ) index. The CQ index is a standardized method for measuring experiences of patients with health care [38]. The questionnaire (T1) includes 30 questions about the experiences of the patients with health care, with specific regard to their experiences with the health-care professionals (e.g. *‘Did you feel welcome and at ease?’* and *‘Did the health-care professionals listen attentively?’*).

Safety of care will be measured using data that will be made available by the hospital concerning: 1) hospital admissions; 2) emergency care visits.

Equity of care will be examined by performing subgroup analysis on all outcome measures regarding educational level (high versus low) and age (lower than median and higher than median).

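### Health is expected to be no worse and safety unchanged, but the only stated test is for a difference and cannot confirm either

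*Protocol article*

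**What the plan says.** **Expectations.** Under Objectives and underlying premises of PC+, the article expects that "the cardiology PC+ centre will result in an (at least) equivalent health of the population". The reason given is that "the cardiology PC+ centre and hospital-based outpatient cardiology care will lead to the same health outcomes". In the same section, "it is supposed that PC+ has no effect on the level of 5) safety of care and 6) equity of care".

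**A different health aim elsewhere.** The Background says "The PC+ intervention aims to improve the health of the population", and the Abstract says much the same. Under Experience of care, the EQ-5D-5L is to be analysed for whether health has improved at 3 months.

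**Measures.** "Safety of care will be measured using data that will be made available by the hospital concerning" hospital admissions and emergency care visits. "Equity of care will be examined by performing subgroup analysis on all outcome measures", by education and by age.

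**Test.** Under Data analysis, "Separate models (random intercept) will be set up for each outcome measure", with group, time and group-by-time terms, and "the level of statistical significance will be set at 0.05 (two-tailed". No equivalence or non-inferiority margin, confidence-interval rule or one-sided test appears in the article. The single sample-size calculation concerns a fall in referrals from 12% to 6%.

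**The concern.** An expectation of no worse is a non-inferiority claim, and an expectation of no effect is an equivalence claim. Both need a statement of how large a deficit would be tolerable. A test of the null hypothesis of no difference has no such quantity. Rejecting that null shows that the groups differ. Failing to reject it may mean that they are alike, or only that the data are too few, too noisy or too incomplete to tell.

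This matters because moving patients out of hospital care is acceptable only if health and safety do not suffer. The Discussion says that the results will lead to recommendations for the pioneer site, which can use them in designing the centre's expansion. Under the stated rule, rare events and dropout make a non-significant result more likely, and that is the result that appears to agree with the premise.

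**Working it through.** **1. The plan's own figure.** Inputs from Sample size and power calculation: p0 = 0.12, p1 = 0.06, p = 0.09, r = 1, z-values 1.96 and 0.84.

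N = (1.96 + 0.84)² × 0.09 × 0.91 × 2 / 0.06² = 356.7 per group.

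The stated 358 is reproduced to within two patients. It powers a difference in referral proportions only and says nothing about health or safety.

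**2. Group sizes used below.** The planned 429 per group applies if outcomes are complete. This may hold for admissions and emergency visits, which come from the hospital's registration system. After the planned 20% dropout, 429 × 0.8 = 343 per group, which suits questionnaire outcomes.

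**3. Safety: chance that a real rise is non-significant.** The article gives no event rates, so these are assumed. For a simple unadjusted two-proportion test:

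power = Φ[(d − 1.96 × SE0) / SE1], where SE0 uses the pooled rate and SE1 the separate rates.

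Example, 5% against 8% with 343 per group:
- SE0 = √(0.065 × 0.935 × 2/343) = 0.01883
- SE1 = √((0.05 × 0.95 + 0.08 × 0.92)/343) = 0.01879
- power = Φ[(0.03 − 0.0369)/0.01879] = 0.36, so the chance of non-significance is 0.64

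| True rates | 343 per group | 429 per group |
|---|---|---|
| 5% to 8% | 0.64 | 0.57 |
| 5% to 10% | 0.30 | 0.20 |
| 10% to 13% | 0.77 | 0.72 |
| 10% to 15% | 0.49 | 0.40 |

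**4. Health: chance that a real deficit is non-significant.** No SD is given, so deficits are in SD units. With 343 per group, SE = √(2/343) = 0.0764 SD. For a deficit d, the chance is about Φ(1.96 − d/0.0764):
- 0.10 SD: 0.74
- 0.15 SD: 0.50
- 0.20 SD: 0.25

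**5. What a non-inferiority reading could support.** With a two-sided 95% interval, 80% power and a true difference of zero, the smallest supportable health margin is (1.96 + 0.84) × 0.0764 = 0.21 SD at 343 per group.

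For safety, n per group = (1.96 + 0.84)² × 2p(1 − p)/margin². With an illustrative margin of 3 percentage points (exact z-values), this needs 829 per group at a 5% event rate, 1,570 at 10% and 2,224 at 15%. All exceed the planned 429.

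**The case against.** **These are premises, and no misuse is stated.** The article calls them underlying premises and gives the quantitative aim as measuring effects. A reader might infer that p > 0.05 will be reported as equivalence, or that policy will rest on it. No sentence says so, and this point does not claim it. What stands is that the article gives no other criterion by which the premises could be confirmed.

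**The 0.05 two-sided level is not wrong.** This is correct. The matching 95% interval is what a non-inferiority judgement would use. The fault is that nothing is set against which to judge it.

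**Margins may be in a fuller document.** They may, and a missing detail alone would not be a finding. But the article itself chooses the test, and that test does not fit the hypotheses it states. Whether the aim is improvement or no worsening is a design-level statement.

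**A difference test fits the wording about improved health.** It does, for that wording. This shows that the health aim is inconsistent and must be settled first. It does not help safety, where no effect is the only stated expectation.

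**Equity already has a method.** Subgroup analyses are planned, so the mismatch is looser there. What remains is that no criterion for an unchanged level is given.

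**The sizes rest on assumed rates.** They do, and they shift with group size. That is why ranges are shown.

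**Conclusion.** The point holds for health and safety, and more loosely for equity. The stated analysis can detect a difference but cannot establish that health is no worse or that safety is unaffected.

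Under the assumed rates, with 343 to 429 per group, a rise in admissions from 5% to 8% would go undetected about 57% to 64% of the time, and a doubling from 5% to 10% about 20% to 30%. At 343 per group, a rise from 10% to 13% would be missed about 77% of the time and a 0.15 SD health deficit about half the time. These figures come from simple unadjusted comparisons, and the event rates and deficits are not from the document.

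It is tempting to add that non-inferiority can be shown comfortably at the current size. The document does not support that, since feasibility depends on a margin that it does not give.

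**What to change.** - **Settle the health aim.** Reconcile the Abstract, Background, Objectives and Experience of care sections, so that the aim is either improvement or no worsening.
- **Health (EQ-5D at T2) and safety (admissions, emergency visits).** State a justified non-inferiority margin for each before the analysis. Conclude no worse only if the adjusted two-sided 95% interval excludes the margin. Otherwise report the result as inconclusive.
- **Equity.** Report group-by-subgroup interaction estimates with intervals, and do not infer an unchanged level from p > 0.05.

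**Cost.** Margins must be agreed and justified before analysis and the conclusions worded to match. The model, the 0.05 level and the number of patients need not change. The price is candour about precision: after the planned dropout, only a health margin of about 0.21 SD or wider has 80% power, and safety may well have to be reported as inconclusive.
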